#### Data analysis

Students are nested within school by time period groups (e.g., 2015 observations of one school), and these repeated observations of a school are each nested within one school. Hence, all quantitative models examining hypotheses will use multilevel modeling (i.e., hierarchical linear modelling) to conservatively adjust estimates for variability arising in outcomes due to student (level 1) nesting within school by time groups (level 2) and these repeated observations at the school level being nested within schools (level 3). Thus, all models will be run as random intercept regressions. Sampling weight and design information will be used to appropriately weight cases in analyses via multilevel pseudo maximum likelihood methods [77, 78] and Mplus^©^ [79]. Models for continuous variables will be run assuming normally distributed, continuous outcomes (unless descriptive analyses indicate zero-inflated Poisson models for count outcomes). Binary outcomes will be treated as having a binomial distribution and use a logit link function. Regression models (one for each measured outcome in all hypotheses) will regress the outcome on a dummy contrast representing study condition; a dummy contrast representing LGB; two contrasts representing linear and quadratic, i.e., u-shaped, change; the orthogonal interactions between condition and change contrasts; the orthogonal interactions between LGB, condition, and change contrasts; and all other component interactions not mentioned. These models represent whether (a) there was differential change as a function of condition and (b) whether this differential change was more pronounced among LGB students.

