### Study design

This 5-year cluster randomized trial will include 40 NM high schools that employ a nurse on staff (*n* = 64). The schools will be randomized into the RLAS intervention condition (IC; *n* = 20) or the control condition (CC; *n* = 20). Cluster randomization was chosen because the intervention will be delivered at the school level. Schools will be eligible if they express interest in the full intervention and the school nurse and a lead administrator agree to participate and support the project. To minimize confounding effects, eligible schools will share the following characteristics: (1) public high school; (2) school nurse willingness to convene an IRT if randomized to the IC group; and (3) informed written consent from the school nurse to participate for four years. Additional file 1 contains confirmation of ethical approval.

From the IC schools, there will be three study populations: (1) school nurses; (2) school administrators; and (3) IRT members. From CC schools, there will be two study populations: (1) school nurses and (2) school administrators. School nurses and IRTs in the IC schools will receive innovation supports to encourage greater implementation of the six EB strategies (see Table 1). Nurses in the IC will recruit IRT members (4–6 people) willing to work with them on implementing the six EB strategies. These nurse champions will function as coordinators who keep the IRTs motivated, cohesive, and focused on goals; gain administrative buy-in during the Preparation Phase; and facilitate IRT planning in the Implementation Phase.

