### Aim 2: conduct a cluster randomized controlled trial to assess whether LGB youth and peers in RLAS intervention schools report reduced suicidality, depression, substance use, and bullying, and increased safety compared to control schools

A cluster randomized controlled trial will assess whether LGBTQ students and their peers in RLAS intervention schools report reductions in suicidality, depression, substance use, bullying, and truancy related to safety concerns compared to those in usual care schools. Additional file 2 provides a study-specific checklist of information to include when reporting a cluster randomized trial. Additional file 3 contains a flow diagram of the phases of the randomized trial for the IC and CC schools. Randomization will take place in the exploration phase, as noted previously. Mahalanobis distance metric matching will be used to create pairs of similar schools [76], where one school in each pair will be randomly assigned to the IC.

The 2015 NM YRRS will offer baseline data for all schools and the 2017 and 2019 NM YRRS will yield follow-up data for the implementation and sustainment phases. From each school an average of 150 students complete the NM YRRS, for a sample size of 6000 per survey administration. Demographic data include gender, age, race/ethnicity, and sexual identity. Primary outcome measures assess suicide-related outcomes (“During the past 12 months, did you ever seriously consider attempting suicide?” “During the past 12 months, did you make a plan about how you would attempt suicide?” “During the past 12 months, how many times did you actually attempt suicide?”). Secondary measures assess depression (“During the past 12 months, did you ever feel so sad or hopeless almost every day for two weeks or more in a row that you stopped doing some usual activities?”), substance use (“During the past 30 days, on how many days did you have at least one drink of alcohol?” “During the past 30 days, how many times did you use marijuana?”), bullying (“During the past 12 months, have you ever been bullied on school property?”), and school safety (“During the past 30 days, on how many days did you not go to school because you felt you would be unsafe at school or on your way to or from school?”).

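### The planned model leaves the arms' 2015 levels free and tests difference-in-change, which is valid but less precise than using the 2015 data as a baseline covariate

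*Protocol article*

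**What the plan says.** The Data analysis section under Aim 2 writes out the fixed part of one regression per outcome. It "will regress the outcome on a dummy contrast representing study condition; a dummy contrast representing LGB". It then adds "two contrasts representing linear and quadratic, i.e., u-shaped, change; the orthogonal interactions between condition and change contrasts", the three-way interactions with LGB, and every remaining component interaction. Random intercepts are placed on school-by-time groups and on schools.

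The target is stated in the same section: "These models represent whether (a) there was differential change as a function of condition", and whether that differential change is stronger in LGB students. The five hypotheses in Aim 2 are worded to match, each as a larger reduction or improvement in intervention schools.

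On the data, Aim 2 says: "The 2015 NM YRRS will offer baseline data for all schools and the 2017 and 2019 NM YRRS will yield follow-up data". It also says: "Demographic data include gender, age, race/ethnicity, and sexual identity". Of these, only sexual identity appears in the listed model. The list contains no school-level 2015 covariate and no constraint of equal 2015 means.

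**The concern.** Three waves with a linear and a quadratic contrast use up all the time degrees of freedom. Crossed with a free condition term, the model fits a separate mean for every arm at every wave. On the linear scale, the condition-by-linear term is then the 2019-minus-2015 change in intervention schools less the same change in control schools.

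Randomisation gives the two arms the same expected 2015 level. A model that estimates a 2015 gap and subtracts it in full carries all the 2015 sampling and school-by-wave error into the effect. A model that uses 2015 as a baseline covariate subtracts only the part that predicts follow-up.

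What is at stake is power, with 40 schools fixed and the data already planned. The loss should be greatest among LGB students, who are the focus of the trial and few in each school, so that each school's 2015 LGB rate is very noisy.

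**Working it through.** **Inputs from the article.** "This 5-year cluster randomized trial will include 40 NM high schools that employ a nurse on staff", 20 per arm. "From each school an average of 150 students complete the NM YRRS, for a sample size of 6000 per survey administration"; this reproduces as 40 × 150 = 6000. The LGB share in Study context is 3.0% + 7.5% = 10.5%, so 150 × 0.105 = 15.75 LGB students per school and wave. The rate of seriously considering suicide is 15.6% overall and 38.3% in LGB students.

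**Assumptions, because the article gives no figure.** ICC 0.005–0.05; correlation c of the true school level between waves 0.5–1.0, the same for any two waves; two-sided alpha 0.05 and 80% power for detectable differences. The calculation works on school means with a normal approximation. It ignores sampling weights, the logit link, unequal school sizes and any gain from pairing.

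**Formulas.** With m students per school and wave, the correlation of a school's observed rate between two waves is

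r = m × ICC × c / (1 + (m − 1) × ICC).

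The variance of the 2019-versus-2015 difference-in-change is proportional to 2(1 − r). With the 2015 school rate as covariate, or equal 2015 arm means by constraint, it is proportional to 1 − r². So planned/alternative variance = 2/(1 + r), which exceeds 1 for every r below 1. Generalised least squares on 40 schools × 3 waves, with free versus constrained baseline, gave the same ratios (for example 1.351 at r = 0.48 and 1.25 at r = 0.60).

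**Results (planned model relative to the alternative).**

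| Group | ICC | c | r | Variance ratio | SE ratio |
|---|---|---|---|---|---|
| All, m = 150 | 0.005 | 0.5 | 0.215 | 1.65 | 1.28 |
| All | 0.01 | 0.8 | 0.482 | 1.35 | 1.16 |
| All | 0.02 | 0.8 | 0.603 | 1.25 | 1.12 |
| All | 0.05 | 1.0 | 0.888 | 1.06 | 1.03 |
| LGB only, m = 15.75 | 0.005 | 0.5 | 0.037 | 1.93 | 1.39 |
| LGB only | 0.02 | 0.8 | 0.195 | 1.67 | 1.29 |
| LGB only | 0.05 | 1.0 | 0.453 | 1.38 | 1.17 |

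One row by hand (all, ICC 0.02, c = 0.8): r = 150 × 0.02 × 0.8 / (1 + 149 × 0.02) = 2.4/3.98 = 0.603; 2/1.603 = 1.25; √1.25 = 1.12.

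A binomial simulation of 20,000 replicates, comparing the two analyses on school means at c = 0.8, gave SE ratios of 1.147 and 1.102 for all students at ICC 0.01 and 0.02. For 16 LGB students per school at ICC 0.02 it gave 1.275. These are slightly below the formula, as expected when the covariate slope must be estimated.

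**In schools.** Multiplying 40 by the variance ratio, the planned analysis would need about 42–66 schools (all students) or 55–77 (LGB only) to match the alternative with 40.

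**In detectable difference, at ICC 0.02 and c = 0.8.** The variance of a school rate is p(1 − p)/m × (1 + (m − 1) × ICC).
- All students: 0.156 × 0.844/150 × 3.98 = 0.003493. Planned SE = √(2/20 × 0.003493 × 2 × 0.397) = 0.01665, times 2.80 = 4.7 points. Alternative: √(2/20 × 0.003493 × (1 − 0.603²)) = 0.01491, or 4.2 points.
- LGB only: the school variance is 0.383 × 0.617/15.75 × 1.295 = 0.01943. The planned SE is 0.05594, or 15.7 points. The alternative is 0.04324, or 12.1 points. Allowing for the degree of freedom spent on the slope (× √(38/37)) makes it 12.3 points.

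**The case against.** The strongest reply is that nothing here is wrong. The hypotheses speak of greater reduction, the model tests differential change, and difference-in-change is valid under randomisation without any equal-baseline assumption. This stands: a reader might infer bias, or a contradiction between model and hypotheses, and the article supports neither. It does not remove the efficiency point, because under randomisation the constrained model targets the same contrast.

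Several limits on stronger readings also stand.
- **Marked loss throughout.** This rests on an ICC and a correlation that the article does not state. For all students the loss is modest to moderate, and close to nil when both are high.
- **Matching.** Schools are paired by Mahalanobis distance, with the matching variables not listed. If 2015 rates are among them, the arms will be close in 2015 by design and the gain is smaller.
- **LGB figures.** They refer to an effect in LGB students alone and apply the same ICC range to them. The planned test is a three-way interaction, whose variance was not computed.
- **Pre-randomisation data.** The article calls 2015 the baseline but does not date randomisation against that survey. The Exploration phase section places randomisation ahead of the initial assessments.
- **No demographic adjustment.** LGB status is in the model. Gender, age and race/ethnicity are not listed, but further covariates may be left to a fuller document, and their gain was not quantified.
- **Exact identities.** The link between the linear term and the 2019-minus-2015 difference is exact on the linear scale. With LGB interactions, the group it describes depends on how LGB is coded. Under the logit link, the constrained and covariate versions are similar but not identical.

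**Conclusion.** The point holds as an efficiency weakness in a model that the article states in full. On the stated assumptions (ICC 0.005–0.05, school-level between-wave correlation 0.5–1.0), the planned standard error is about 3–28% larger than necessary for all students, and 10–16% at middle values. For an LGB-only effect it is about 17–39% larger. The direction holds for any correlation of observed school rates below 1. The size depends on quantities the article does not give, and on how closely pairs were matched on 2015 rates. The planned analysis remains valid, so this is a change that should be made, not a fault that undermines the trial.

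**What to change.** Code the waves as indicators with 2015 as reference. Drop the condition and LGB × condition main effects, so that the arms share a common 2015 mean within LGB and non-LGB students. Keep condition × 2017, condition × 2019 and their LGB interactions. Alternatively, model the 2017 and 2019 outcomes with the school's 2015 rate as a covariate.

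Before adopting either, confirm that the 2015 survey preceded any intervention effect; the equal-mean constraint depends on it. For logit models, also report a marginal effect, since covariate adjustment changes the conditional odds ratio. Prespecifying gender, age and race/ethnicity as student-level covariates is an optional addition of unquantified gain.

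The cost is a change of analysis wording; every variable is already collected. It should be fixed before the follow-up outcomes are analysed, so that the adjustment cannot appear to have been chosen from the data.

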### Aim 3: examine the individual, school, and community factors influencing implementation and outcomes

For the RLAS process evaluation, school health policies, practices, and community linkages, and the status of EB strategies will be assessed and compared across IC and CC groups. This will be done annually each spring via semi-structured interviews with all school administrators (*n* = 40) and nurses (*n* = 40) in years 1–4. To assess individual and school influences, the web-based surveys will be repeated with IC and CC groups each year. All qualitative interviews and surveys will follow the data collection and analysis procedures used in the preparation phase. Using these same qualitative analysis procedures, the content of coaching logs that describe in-depth implementation issues requiring technical assistance in the IC schools over the intervention period will also be assessed. Analysis of the web-based surveys aggregated across IC and CC schools will help identify and compare differences in the organizational characteristics of schools and administrator/nurse work attitudes over time.

#### Data collection and analysis

Many schools may already utilize one or more EB strategy; yet use of all six in accordance with CDC specifications is uncommon [40]. There is also a need to assess potential diffusion of the RLAS to CC schools. The EB strategy implementation in all 40 schools will be tracked using the adapted ACEM incorporated into the annual web-based surveys completed by nurses and administrators [43]. This instrument will yield data on frequency of EB strategy usage, EB strategy adherence, and school leadership support. These data will be supplemented with descriptive information from qualitative interviews concerning the extent to which the RLAS may stimulate changes in implementation, diffusion, and overall implementation status of each EB strategy at each school.

Implementation progress and fidelity for each EB strategy in IC schools will be determined via a modified version of the *Stages of Implementation Completion* (SIC) checklist, an eight-stage measure that will assess progress for phases of pre-implementation (exploration/preparation), implementation, and sustainment using activity completion dates and duration of activities and does not require additional effort from the school nurse champions and IRTs beyond participating in the usual implementation process [80]. The research team will complete the SIC by coding data from interviews, surveys, action plans, and coaching logs concerning markers or milestones. These data sources offer insight into individual, school, and community factors affecting progress. The SIC will be adapted to capture key stages of implementation progress for the six EB strategies. These may include the following: (1) engagement; (2) consideration of feasibility; (3) readiness planning; (4) staff trained; (5) fidelity monitoring process in place; (6) implementation begins; (7) ongoing implementation, coaching, and feedback; and (8) competency. The SIC scores will indicate the level of RLAS implementation per IC school over time, allowing categorization of the IC schools into “low” versus “high” implementation sites. These categories will be used to organize analyses of qualitative data to determine characteristics shared among IC schools assigned particular scores and to describe common barriers and facilitators that may have affected their implementation progress.

During the implementation and sustainment phases, the research team will conduct annual focus groups with the 20 IRTs to document their common and particular experiences identifying and advancing adaptation supports to facilitate use of EB strategies and their overall progress and satisfaction with the DAP. Each focus group will consist of at least five IRT members (including the school nurse), take place on site when IRTs regularly meet, and last between 90 to 120 min. Members will complete demographic forms (recording age, gender, sexual orientation, race/ethnicity, education, employment, socioeconomic status, religion, etc.) and a 10-min survey on individual perceptions and experiences related to the IRTs and the DAP. The focus group guides will consist of eight to ten open-ended questions. Participants will be asked to reflect on satisfaction, EB strategy implementation (including contextual relevance, feasibility, strategies to overcome barriers, and processes for forging and maintaining local linkages with health, mental health, and LGBTQ resources), and perceived outcomes on students, schools, and communities. These collective discussions [81, 82] will illuminate factors influencing the ability of IRTs to maintain their original action plans, reasons for possible divergence from these plans (e.g., community resistance) and subsequent adaptations (community education), and provide insight into possible changes to school climate, safety, support, and minority stress for LGBTQ students in IC schools. Using iterative coding, responses on perceived strengths, weaknesses, adaptations, and needed improvements will be clustered.

Convergences and divergences in quantitative and qualitative data will be identified [83–86]. Analyses of survey, NM YRRS, ACEM, and SIC data will be summarized, and findings from different data sources will be compared to create a complete picture of DAP and EB strategy implementation in the IC schools over time. Results will be integrated through an inclusive process that values the input of all stakeholders (nurses, administrators, and IRT members). Data will be merged by the following: (a) linking qualitative and quantitative databases; and (b) embedding one within the other so that each plays a supportive role for the other. Results of each dataset will be placed side-by-side to examine: (1) *convergence* (do results provide the same answer to the same question, e.g., do interview data concur with NM YRRS data regarding impact of RLAS on suicide risk among LGBTQ students?); (2) *expansion* (are unanticipated findings of one dataset explained by another, e.g., can web-based survey data that suggest a disempowering school climate be explained by qualitative interview data?); and (3) *complementarity* (does embedding results of the qualitative analysis in the quantitative dataset help contextualize results, e.g., does it explain variability represented by confidence intervals or variance estimates in statistical analyses on “bullying on school grounds” and “fear-based bullying”?). Triangulated results will be shared annually with IRTs and schools.

## Discussion

The RLAS keeps with national priorities to (a) improve school-based services for pediatric populations, (b) focus on LGBTQ youth mental health, and (c) revolutionize the role of nurses in U.S. healthcare. In addition to LGBTQ youth suicide, the conceptual framework and methods for this novel nurse-led intervention are applicable to addressing the health-related concerns of other pediatric populations in schools as well. Through its collaborative processes to refine, improve, and sustain EB strategies in these systems, the RLAS represents an innovative contribution to implementation science that also addresses a pressing public health challenge.

## Abbreviations

ACEM: Assessment of Climate Embedding Mechanisms
CC: Control condition
CDC: Centers for Disease Control and Prevention
DAP: Dynamic Adaptation Process
EB: Evidence-based
GSA: Gay-Straight Alliance
IC: Intervention condition
IRT: Implementation Resource Team
LGB: Lesbian, gay, and bisexual
LGBTQ: Lesbian, gay, bisexual, transgender, and queer or questioning
MLQ: Multifactor Leadership Questionnaire
NM: New Mexico
RLAS: Implementing School Nursing Strategies to Reduce LGBTQ Adolescent Suicide
SIC: Stages of Implementation Completion
YRRS: Youth Risk and Resiliency Survey
